## Abstract

**Background:**

Hip osteoarthritis (hip OA) is a disease with a major impact on both national economy and the patients themselves. Patients suffer from pain and functional impairment in activities of daily life which are associated with a decrease in quality of life. Conservative therapeutic interventions such as physical exercises aim at reducing pain and increasing function and health-related quality of life. However, there is only silver level evidence for efficacy of land-based physical exercise in the treatment of hip OA. The purpose of this randomized controlled trial is to determine whether the specific 12-week exercise regime "Hip School" can decrease bodily pain and improve physical function and life quality in subjects with hip osteoarthritis.

**Methods/Design:**

217 participants with hip OA, confirmed using the clinical score of the American College of Rheumatology, are recruited from the community and randomly allocated to one of the following groups: (1) exercise regime "Hip School", n = 70; (2) Non-intervention control group, n = 70; (3) "Sham" ultrasound group, n = 70; (4) Ultrasound group, n = 7. The exercise regime combines group exercises (1/week, 60-90') and home-based exercises (2/week, 30-40'). Sham ultrasound and ultrasound are given once a week, 15'. Measures are taken directly prior to (M1) and after (M2) the 12-week intervention period. Two follow-ups are conducted by phone 16 and 40 weeks after the intervention period. The primary outcome measure is the change in the subscale *bodily pain *of the SF36 from M1 to M2. Secondary outcomes comprise the WOMAC score, SF36, isometric strength of hip muscles, spatial-temporal and discrete measures derived from clinical gait analysis, and the length of the centre of force path in different standing tasks. An intension-to-treat analysis will be performed using multivariate statistics (group × time).

**Discussion:**

Results from this trial will contribute to the evidence regarding the effect of a hip-specific exercise regime on physical function, pain, and health-related quality of life in patients with hip osteoarthritis.

**Trial registration:**

German Clinical Trial Register DRKS00000651.

## Background

### Prevalence and treatment modalities of osteoarthritis

Osteoarthritis (OA) is a disease with a major impact on both the national economy and the patients themselves. In Germany, approximately five million people suffer from osteoarthritis [1]. It is the most prevalent musculoskeletal disease and its impact on morbidity and mortality in industrialized countries is almost as large as the impact of respiratory or digestive disorders [2]. The knee and hip joints are the most commonly affected joints of this disease [1,3]. Data from a large cohort-study reveal hip symptoms in 36% of an American population aged 45 and older. 28% of this population had radiographic, and 10% had symptomatic hip OA [4]. Prevalence for symptomatic hip OA increases in older individuals and women [4]. According to demographic estimates, more than 20% of the population will be older than 65 years in 2040 [5], and the impact of OA will further increase. Patients suffer from pain and functional impairment in activities of daily life such as walking or climbing stairs [6,7]. Strength deficits and gait disturbances like gait asymmetries and reduced walking speed are frequent findings [8-10]. Bodily pain and deficits in physical functioning are associated with a decrease of life quality [7,11].

Joint replacement is the treatment strategy in the final stages of hip or knee OA. In earlier stages, conservative therapeutic interventions are important to reduce pain and increase function and health-related quality of life [12]. In this respect, physical therapy and physical exercise programs are relevant and important therapeutic options. Here, treatments during which the patient is active are preferable to passive therapies [13,14]. Physical exercises in particular are non-hazardous in terms of side-effects and can have positive effects on life quality, management of everyday life and physical functioning [15-19]. Exercises can further decrease pain and their efficacy was shown to be comparable to the efficacy of non-steroidal anti-inflammatory drugs (NSAIDs). In addition, they do not have expected adverse reactions in comparison to the long term use of NSAIDs [14,20].

### Evidence for effectiveness of exercises in the treatment of lower limb osteoarthritis

Platinum/1a level of evidence is given for the efficacy of joint related exercise programs with respect to pain reduction and increase of function in subjects with knee OA. It applies to analyses including data of aquatic and land-based exercises, as well as for land-based exercises only [21,22]. According to the EULAR evidence based recommendations for the management of hip osteoarthritis published in 2004, data on exercise interventions for hip OA are required to determine the benefit of treatments at each key site of OA, as there may be true treatment differences for OA according to the site affected [23]. More recently, meta-analyses have been published focusing explicitly on the effects of exercise on hip osteoarthritis. Combined data of aquatic and land-based exercises for hip OA demonstrate evidence (1a) for the reduction in pain [24,25]. However, there is only silver-level evidence for the efficacy of land-based physical exercise to reduce pain and to improve function in the treatment of hip OA [26]. The aforementioned review summarizes the effects of only five randomized controlled trials (RCTs) which were included into the meta-analysis. Only one of these studies explicitly focused on patients with hip osteoarthritis. The authors conclude that the limited number and small sample size of the included RCTs restricts the confidence that can be attributed to the presented results. Therefore, adequately powered RCTs evaluating exercise programs specifically designed for people with symptomatic hip OA need to be conducted [26].

Aside from a lack of large RCTs studies on subjects with hip OA, there is not much known about how an optimised training program should be designed and what kind of training would be the most efficient for treating hip and knee OA [19,27,28].

### Hip School

The group exercise program "Hip School" was established in 1996 [29,30]. Since then, more than 20 therapy groups have been organized in the region allowing many patients with hip osteoarthritis access to a supervised training program. Several studies were conducted previously to evaluate the efficacy of the Hip School [31-34]. However, its efficacy has not yet been demonstrated in a randomised controlled trial using generally accepted measures. This lack of evidence is being addressed by the clinical trial described in this study protocol. The protocol is based on (a) previous pilot studies investigating the reliability, validity, and feasibility of the methods that will now be used to quantify efficacy outcomes in subjects with hip osteoarthritis [35-37], and (b) an interventional study used to quantify efficacy and feasibility of an additional home-based exercise program in combination with the aforementioned therapy regime [38-40].

### Study purpose

The primary aim of this study is to determine whether a 12-week intervention program comprising group and home-based exercises decreases bodily pain in subjects with hip osteoarthritis in comparison to a non-treated control group. Efficacy is quantified by the subscale *bodily pain *of the SF36. The secondary aim is to determine whether this exercise regime can improve function, health-related quality of life, strength of hip surrounding muscles, postural control in bi-pedaled, tandem-, and single leg stance, joint function, and gait parameters in comparison to a non-treated control group, an attention control group (sham ultrasound), and an ultrasound group. Ultrasound therapy is only investigated in an explorative manner. Follow-up data are recorded to evaluate the sustainability of the interventional programs over another 40 weeks.

It is hypothesized that a 12-week intervention program will (1) decrease pain, and (2) improve physical function in comparison to a non-treated control. It is further hypothesized that (3) the efficacy of the exercise regime is superior to the efficacy of an intervention solely aiming for attention control, and (4) that effects are long-acting.

## Methods/Design

### Design

This is a randomized, controlled trial, single-blinded for participants for two of the four treatment options (sham ultrasound and ultrasound) (Figure 1). Recruited patients undergo telephone screening followed by a clinical examination by a medical doctor to ensure eligibility. Eligible participants then undergo outcome assessment using the complete test battery prior to intervention, and will subsequently be randomized to one of the four groups. A ratio of 10:10:10:1 will be used for randomization into Hip School (HS), no intervention group (CO), sham ultrasound group (SUS), and ultrasound group (US). During the 12 week intervention period, monthly logbooks for physical exercises and pain have to be completed by all subjects. The complete test battery is repeated after the 12 week interventional period. Questionnaires (WOMAC, SF36) and log books are accessed via telephone assessment 16 and 40 weeks after the retest.

**Figure 1 F1:**
[figure not shown]
**Trial protocol**.

### Randomization process and allocation concealment

Randomization is stratified by gender due to its possible influence on efficacy of strengthening exercises [41,42]. Since not all subjects can be measured and treated simultaneously, the study is divided into four identical interventional periods (sequence 1-4), and the mentioned allocation procedure is performed in permuted blocks of 50-60 subjects each. The randomization sequence is generated electronically prior to each interventional period. Participants draw a lot with a randomization number at the beginning of baseline assessment. This process is double-blinded (participant and investigator). At the end of the baseline assessment, a study nurse compares the randomization number of the lot with the randomization list displaying information on treatment allocation. Group allocation is then documented on an extra sheet of the case report form. The case report form is filed after baseline assessment. The assignment process as described prevents foreknowledge of treatment assignment.

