### Proposed sample size/power calculation

The primary endpoint is the change of SF36: Subscale bodily pain from M1 to M2 of HS in comparison to CO. Responsiveness of the subscale is comparable to the pain scale of the disease specific WOMAC in patients with osteoarthritis undergoing a rehabilitation intervention [52]. The SF36 is recommended as a generic instrument for recording relevant domains in osteoarthritis of the lower limb [53]. It is the most widely used generic health instrument [52] and allows comparison of disease states within and between different disorders.

Sample size calculation is based on clinically relevant changes: An effect smaller than the minimum clinical important difference (MCID) may be measureable although patients will be unable to notice it [50]. MCID was derived from literature [50], basic values and statistical spread of the measure for the given population were derived from a pilot study of our own research group on subjects with hip osteoarthritis. According to the mentioned presumptions, a sample size of n = 60 in each group will have 80% power to detect a clinically relevant difference in bodily pain for HS in comparison to CO using a two group t-test with a 0.05 two-side significance level. A failure rate of 15-20% is approximated, thus final sample size is set at n = 70 for each group, except US with n = 7. This is only an explorative intervention. Sample size was calculated using G*Power Version 3.0.10 (Franz Faul, Universitaet Kiel, Germany).

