### Statistical analysis

Data will be analyzed on an intention-to-treat principle using all randomized participants. Missing data will be filled in by carrying the last score forward. A per protocol analysis will also be conducted as a subordinate type of analysis. Demographic characteristics, joint and muscle function, and logbooks will be displayed with descriptive statistics. Multivariate statistics will be used (factors: group × time) for outcomes measured on a continuous scale. For strength measures, baseline levels will be included as covariates.

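### The stated group × time model leaves out gender and period, the two factors that restrict the randomisation, so the analysis does not reflect the design and may give up some precision

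*Protocol article*

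**What the plan says.** The protocol article's section on randomization and allocation concealment sets two restrictions on allocation. The first is gender: "Randomization is stratified by gender due to its possible influence on efficacy of strengthening exercises [41,42". The second is time: "the study is divided into four identical interventional periods (sequence 1-4", and "The randomization sequence is generated electronically prior to each interventional period". Within this scheme, "the mentioned allocation procedure is performed in permuted blocks of 50-60 subjects each". The Design section gives the ratio: "A ratio of 10:10:10:1 will be used for randomization into Hip School (HS), no intervention group (CO" and onward to the two ultrasound arms, which makes Hip School versus control 1:1.

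The Statistical analysis section gives the model: "Multivariate statistics will be used (factors: group × time) for outcomes measured on a continuous scale". The only covariate it names is baseline, and only for one family of outcomes: "For strength measures, baseline levels will be included as covariates". The abstract also gives group × time. The sample size section defines the endpoint, "The primary endpoint is the change of SF36: Subscale bodily pain from M1 to M2 of HS in comparison to CO", and powers it with an unadjusted two-sample t-test. Gender and period appear in none of these analysis statements.

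**The concern.** A factor used to restrict randomisation normally belongs in the analysis. When the arms are balanced on a factor that predicts the outcome, that factor's variance no longer contributes to the treatment contrast. If the model omits the factor, the same variance still sits in the residual. The standard error is then larger than the design warrants, and the precision that stratification was meant to secure is not collected.

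Here the protocol chose gender because it may affect the response to exercise, and it randomised each period separately, yet the stated model uses neither. At stake is a modest amount of power in a trial with little to spare: after the expected losses, 70 per group leaves slightly fewer than the 60 on which the 80% rests.

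**Working it through.** **1. The plan's own figure.** The sample size section gives n = 60 per group, 80% power and two-sided 0.05 with a two-sample t-test. It prints neither the clinically important difference nor the SD, so 60 cannot be reproduced from its inputs. Solving backwards, it implies a standardised difference of d = 0.516 (0.511 by the normal approximation). With 70 per group and 15–20% failure, 70 × 0.85 = 59.5 and 70 × 0.80 = 56 remain.

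**2. Cost of omitting balanced factors.** Let R² be the share of variance in the M1–M2 change explained by gender and period, with arms balanced within strata. R² is an assumption, because the article gives no value.

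- Excess interval width without adjustment: 1/√(1 − R²) − 1
- Actual type I error without adjustment: 2 × [1 − Φ(1.96/√(1 − R²))]
- Power with adjustment: the t-test at n = 60 per arm with d/√(1 − R²), d = 0.516

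| Assumed R² | Excess width | Type I error | Adjusted power |
|---|---|---|---|
| 0 | 0% | 5.0% | 80.0% |
| 0.02 | 1.0% | 4.8% | 80.8% |
| 0.05 | 2.6% | 4.4% | 82.0% |
| 0.10 | 5.4% | 3.9% | 84.0% |

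For R² = 0.10: √0.90 = 0.9487, 1/0.9487 = 1.054, 1.96/0.9487 = 2.066, and the two-sided tail beyond 2.066 is 0.039.

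**3. Simulation check.** With eight gender-by-period strata, 60 per arm and 5,000 runs per scenario, the unadjusted-to-adjusted width ratio under balance was 1.00, 1.01, 1.03 and 1.05 at the four R² values. Coverage of the unadjusted 95% interval under no effect was 95.3%, 95.8%, 95.6% and 96.3%.

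**4. Is balance assured?** The ratio 10:10:10:1 sums to 31, so a block that holds it exactly must be a multiple of 31. The multiples nearest the stated range are 31 and 62; none lies from 50 to 60. A period averages 217/4 = 54.25 people, about one block. If blocks of that size were applied within each gender, they would not be filled. Balance within gender-by-period strata is therefore uncertain. In the simulation without that balance, at R² = 0.10, unadjusted coverage was 94.5%, nominal within simulation error. The unadjusted interval was still 3.6% wider than the adjusted one, so it is valid but less efficient.

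**5. Level or change?** With two time points and complete data, the group × time contrast is the difference between arms in mean change. A gender or period effect that shifts M1 and M2 equally cancels in each person's change. In one simulated sample where gender affected level only, the SE for change was 0.202 unadjusted and 0.204 adjusted, so there was nothing to gain. Only an effect on change counts towards R².

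**6. Which terms help?** By the same cancellation, main effects of gender and period in a group × time model cannot alter the group × time standard error. In one simulated dataset where both factors affected level and change, the SE was 0.1690 for group × time alone, 0.1690 with main effects added, and 0.1651 with both factors crossed with time.

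**The case against.** A reader might infer from the mismatch that the trial's intervals are simply too wide. The document does not support that. The over-width needs gender or period to predict the change in bodily pain, and it needs balance within strata. The article gives no predictive strength for either factor, R² could be zero, and the block arithmetic leaves the balance in doubt. The stated reason for stratifying concerns response to strengthening exercise. That is effect modification, most plausible for strength in the exercise arm. It makes some effect of gender on change plausible but does not show that gender predicts pain change across arms.

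Nor can one conclude that season, staff and class differences remain as noise in every outcome. Period differences in level cancel in the change. The article describes the periods as identical and, for strength testing, says one investigator always gives the instructions. Exercise classes exist only in the Hip School arm. With at most 15 per group and 70/4 = 17.5 Hip School participants per period, a period would usually hold more than one class, and a period term does not remove that clustering. These points stand.

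It can also be said that a condensed article leaves the covariate list to an analysis plan that is not shown. That carries only part of the way. The article does more than stay silent: it names the model factors and one covariate, and the randomisation factors are not among them. A fuller plan may add them, but the model as published does not match the design.

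**Conclusion.** The point holds in conditional form. Allocation is restricted by gender and by period, and the stated model for continuous outcomes contains neither. To the extent that these factors predict change and balance is achieved, the unadjusted test is mildly conservative: across an assumed R² of 0 to 0.10, the excess width is at most 5.4%, type I error falls no lower than 3.9%, and the power forgone is at most 4 points at 60 per arm. Where balance fails, the unadjusted analysis is valid and only less efficient. It would be wrong to read this as bias or as an inflated false-positive rate. The mismatch is certain. Its size rests wholly on the assumed R², and at the low end it is nil.

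**What to change.** Add gender and period (sequence 1–4) to the primary Hip School versus control analysis and to the other continuous-outcome models, in one of two ways:

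- as covariates in a model for the M1–M2 change, or for the M2 score with baseline as a further covariate; or
- crossed with time, if the group × time model is kept. Main effects alone would leave the group × time standard error unchanged.

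The cost is about four degrees of freedom for the treatment contrast (one for gender, three for period). Gender is recorded at baseline, and period is known from the randomisation list. The text change is small, but it must say which of the two forms applies. A group-by-gender interaction may be reported as exploratory, since the protocol raises gender as a possible influence on efficacy; it is optional.

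The block size and the 10:10:10:1 ratio should also be reconciled in the text, because the precision that stratification buys depends on the balance achieved.

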### Participants

217 men and women aged between 18 and 85 years are recruited via regional press, flyers in medical and physiotherapeutic practices, the outpatient clinic of the Department of Sports Medicine, and personal communication. Eligibility is confirmed by verbal and clinical examination carried out by the principal investigator of the study (medical doctor). Criteria for hip osteoarthritis are defined according to the clinical criteria of the American College of Rheumatology [45]. Other inclusion criteria are: (i) health-related eligibility in terms of physical and mental ability to participate in the interventional program; (ii) sufficient time to keep therapeutic appointments; (iii) capacity to consent. Annotation: Subjects can also be included in the case of a contra-lateral hip replacement, as long as one side has a hip osteoarthritis according to the above mentioned criteria.

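### Permuted blocks of 50-60 cannot hold the 10:10:10:1 ratio, and at about the size of a whole period they do not secure the stated balance by gender (minor)

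*Protocol article*

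**What the plan says.** Four statements in the protocol article bear on this.

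- **Ratio** (Design): "A ratio of 10:10:10:1 will be used for randomization into Hip School (HS), no intervention group (CO), sham ultrasound group (SUS), and ultrasound group (US").
- **Stratum** (Randomization process and allocation concealment): "Randomization is stratified by gender due to its possible influence on efficacy of strengthening exercises".
- **Periods, blocks and lists** (same section): "the study is divided into four identical interventional periods (sequence 1-4"), and "the mentioned allocation procedure is performed in permuted blocks of 50-60 subjects each". It adds that "The randomization sequence is generated electronically prior to each interventional period".
- **Size** (Participants; Proposed sample size/power calculation): "217 men and women aged between 18 and 85 years are recruited", and the "final sample size is set at n = 70 for each group, except US with n = 7".

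The article does not say whether a block of 50-60 is a whole period's intake or one gender's list within a period.

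**The concern.** A permuted block gives two things: it holds the ratio exactly when it is complete, and it limits imbalance within each stratum. The first needs a block size that the ratio divides. The second needs blocks small enough to be completed, or nearly so, inside a stratum. The stated range appears to fail on both counts.

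At stake are the arm sizes, above all the small ultrasound arm, and the gender mix of the arms. Gender was made a stratum because it may influence how well strengthening exercise works, so a rule that loosens gender balance weakens a protection that the authors chose on purpose.

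**Working it through.** **1. The plan's own totals.** 10 + 10 + 10 + 1 = 31. 70 + 70 + 70 + 7 = 217 = 7 x 31. Total, arm sizes and ratio agree with one another.

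**2. Ratio against block size.** The multiples of 31 nearest the range are 31 and 62; none lies in 50-60. Exact shares would be:

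- per large arm: 50 x 10/31 = 16.1 up to 60 x 10/31 = 19.4;
- ultrasound: 50/31 = 1.6 up to 60/31 = 1.9.

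These are not whole numbers, so no single block can hold 10:10:10:1. This step needs no assumption.

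**3. Are the totals still reachable?** Yes, if composition differs between blocks. Example: 53 (17/17/17/2) + 53 (17/17/17/2) + 56 (18/18/18/2) + 55 (18/18/18/1) = 217 = 70/70/70/7. With the three large arms equal in each block, 25 sets of four blocks of 50-60 reach these totals with 1-3 US places per block, and 9 do so with only 1 or 2.

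**4. Gender against block size.** A period averages 217/4 = 54.25 people. Completing one block per gender per period needs at least 2 x 50 = 100. The share of women is not stated; I take 50% to 70% as an assumption. A period of 50-60 then has 25-42 women and 15-30 men, so neither gender fills a block.

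**5. Reading A: one block per gender, restarted each period.** Take a 56-place block (18/18/18/2). If n of N places are used and each of HS and CO has k places, then

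Var(HS - CO) = n x (2k/N) x (N - n)/(N - 1).

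- 50% women, n = 27 in each of eight cells: 27 x (36/56) x 29/55 = 9.15; 8 x 9.15 = 73.2; SD = 8.6.
- 70% women, n = 38 and 16: 7.99 and 7.48; 4 x (7.99 + 7.48) = 61.9; SD = 7.9.

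Simulation (5,000 trials) gives SD 7.8-8.5, a 95th percentile of the absolute difference of 15-17, and a 95% range for US of 4 to 11 or 12. The HS-CO difference in share of women has SD about 6 percentage points, so gender is partly balanced. For scale, simple randomisation gives an HS-CO count SD of 11.9.

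**6. Reading B: one block for the whole period, both genders together.** Totals can be exactly 70/70/70/7 (step 3), but gender is left to chance. With share f of women, the SD of the HS-CO difference in share is about sqrt(2f(1 - f)/70): 8.5 points at f = 0.5 and 7.7 at f = 0.7. Simulation gives 7.9-8.5, with a 95th percentile of 16-17 points.

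**7. Reading C: 50-60 is the period cohort, with gender sub-lists inside it.** If the sub-lists are sized to each gender's intake, simulation (8,000 trials) gives an HS-CO count SD of 1.9, no gap of 10 or more, and US = 7. What remains is mainly rounding.

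**8. Blocks of 31 per gender, running on across periods.** Only the last block in each gender stays open.

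- 50% women (108 and 109): 15 and 16 places used in the open blocks; variance 5.16 + 5.16 = 10.3; SD = 3.2.
- 70% women (152 and 65): 28 and 3 places used; 1.81 + 1.81 = 3.61; SD = 1.9.

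Simulation agrees (1.9-3.2), with US 6-8 and an SD for the difference in share of women of 1.4-2.3 points.

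**9. Power.** The plan gives n = 60 per group, 80% power and two-sided 0.05, but not the difference or SD. Back-solving by the normal approximation gives a standardised difference of 0.511. At 52 against 68, 0.511/sqrt(1/52 + 1/68) = 2.78, and power = Phi(2.78 - 1.96) = 79.3%, against 80.0% at 60/60.

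**The case against.** The ratio is stated for the trial, not for each block, and 70/70/70/7 meets it exactly. A split such as 17/17/17/2 is whole-number rounding for an intake of 50-60. Four times 50-60 is 200-240, which contains 217, so the range looks like a period's cohort, and the block sentence refers back to the gender-stratified procedure. Gender lists inside the cohort (reading C) would remove nearly all of the imbalance. A condensed article may leave such detail to the full protocol. The ultrasound arm is only exploratory. Blocks of 31 would not be perfect either: they reach exactly 70/70/70/7 in only 6-15% of simulated trials, and they do not fix arm numbers within a period.

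Much of this stands. A reader might infer that four identical periods can yield only 4 or 8 ultrasound participants and never 7, so that the planned allocation cannot be delivered. The article does not support that: it calls the interventional periods identical, not the composition of the blocks, and block size may vary. A reader might also take the large imbalances of reading A as what the document prescribes. They follow from one reading that it does not state.

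What does not fall away is that reading C is not stated either. The article itself chose to give ratio, stratum, block size and list timing, and as written they do not combine into one rule that can be carried out.

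**Conclusion.** The point holds as a minor one. It is certain that no block of 50-60 can carry 10:10:10:1, and that blocks of that size cannot be completed in both genders within a period of about 54. The exact ratio within blocks and the gender balance are therefore not guaranteed; it would go too far to say that they fail.

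The size depends on the reading and on an assumed 50-70% women. Under gender-specific blocks, the HS-CO count SD is about 8 and US is about 4 to 12. Under whole-period blocks, totals can be exact, but the HS-CO difference in share of women has SD about 8 points. Under cohort sub-lists, little beyond rounding remains.

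The loss of primary power is negligible (80.0% to 79.3% even at 52 against 68). Nothing here suggests bias or a failure of concealment: allocation stays random, and the lot is matched to the list only at the end of the baseline assessment.

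**What to change.** Correct the block sentence. Use blocks of 31 (10 HS, 10 CO, 10 SUS, 1 US) within each gender, on one list per gender that continues through all four periods instead of restarting. Since 217 = 7 x 31, this gives 70/70/70/7 to within one open block per gender (HS-CO SD about 2-3, US 6-8).

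If 50-60 was meant only as the period cohort with gender sub-lists inside it, say so and state how places are divided between the arms in each sub-list.

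The cost is one changed sentence and regeneration of any lists not yet used. There are two small downsides. A shorter block is slightly more predictable near its end, which matters little because allocation is revealed only after baseline. Arm numbers within a single period would also no longer be fixed exactly.
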